#### PAT reactive hyperemia index as a measure of vascular endothelial function:

Technique: Reactive hyperemia index of the finger will also be measured simultaneously with FMD measurement as described above. With the patients in the supine position in a temperature controlled room with both hands at the same level, PAT (Itamar Inc.) probes, one on each hand and at the same finger (fingers 2, 3 or 4) will be placed (Please also see section C 2 above). The blood pressure cuff will remain on one hand (the study arm) and the other arm will serve as a control. Following the 10-minute equilibration period, the blood pressure cuff is inflated to 60 mmHg above systolic pressure for 5 minutes with continuous recording. This is followed by deflation of the cuff and continuous recording from both arms for 5 minutes. Reactive hyperemia index (RHI) is calculated as a ratio of hyperemic to baseline flow signal.

**Measurement of Arterial Stiffness/Compliance:** Technique: Vascular function will be assessed as pulse wave velocity and radial pulse wave analysis measured noninvasively using the SphygmoCor® Pulse Wave Velocity system (PWV Medical, NSW, Australia). In brief, peripheral pressure waveforms are recorded from the radial artery at the wrist, using applanation tonometry with a high-fidelity micromanometer. After 20 sequential waveforms have been acquired, a validated generalized transfer function will be used to generate the corresponding central aortic pressure waveform.

The augmentation index: The SphygmoCor is a computerized, portable and simple-to-use device used to assess pulse waveforms. Aortic pulse waveform, augmentation index, and central aortic pressure will be derived at the radial artery by applanation tonometry. Only high-quality recordings, defined as an in-device quality index  $>80\%$  (derived from an algorithm including average pulse height, pulse height variation, diastolic variation, and the maximum rate of rise of the peripheral waveform) and acceptable curves on visual inspection by the PI will be included in the analysis. Studies with inadequate tracings will be excluded. All pulse wave analyses will be taken in the sitting position in a quiet room after a brief period (at least 15 minutes) of rest. Augmentation index (Aix) and augmented pressure (AP) will be derived from this with the technique of pulse wave analysis. The merging point of the incident and the reflected wave (the inflection point) is identified on the generated aortic pressure waveform. AP is the maximum

systolic pressure minus pressure at the inflection point. The AIx is defined as the AP divided by pulse pressure and expressed as a percentage. Larger values of AIx indicate increased wave reflection from the periphery or earlier return of the reflected wave as a result of increased pulse wave velocity (attributable to increased arterial stiffness) and vice versa. In addition, because AIx is influenced by heart rate, an index normalized for heart rate of 75 bpm (AIx@75) will also be used in accordance with Wilkinson et al. Time to return of the reflected wave (Tr) is the time from the beginning of the derived aortic systolic pressure waveform to the inflection point and can be used as a substitute for pulse wave velocity (a higher pulse wave velocity will lead to a shorter Tr).

Pulse wave velocity measurement: The pulse wave velocity (PWV) system measures the velocity of the blood pressure waveform between any two superficial artery sites. It uses a single-lead electrocardiogram and then a tonometer to measure the pressure pulse waveform sequentially in the two peripheral artery sites. Transcutaneous Doppler flow velocity recordings will be carried out simultaneously at the base of the neck over the common carotid artery and the femoral artery in the groin with the PWV system attached to a laptop computer (SphygmaCor). The time delay (t) will be measured between the feet of the flow waves recorded at these points. The distance (d) traveled by the pulse wave is measured over the body surface as the distance between the two recording sites minus that from the suprasternal notch to the carotid artery recording site. PWV is calculated as  $PWV=d/t$ . The reproducibility of the measurement for aortic PWV has been published previously.

Reproducibility and experience: We are currently conducting an NIH funded study in a multi-ethnic community population of 1000 subjects who are all having arterial compliance assessed in this manner. Three technicians have been trained to conduct these measurements reliably and reproducibly. The mean difference between consecutive AIx and AP measurements performed on 2 different days of 1.37% and 1.2 mm Hg, respectively; 95% limits of agreement for AIx and AP were 10.1% and 9.6 mm Hg, respectively.

Autonomic Measurements: We will assess measures of sympathetic and parasympathetic tone to acute mental stress using the VU AMS holter device (VU University, Netherlands) and plasma catecholamines. The VU AMS device measures ECG and impedance cardiography simultaneously, which allows for the measurement of the pre-ejection period (PEP), a measure of cardiac sympathetic function. PEP is quantified as the difference in time between R wave peak and the opening of the aortic valves. More details on the exact methods used to calculate PEP using the VU AMS device are described elsewhere. For parasympathetic tone, high frequency heart rate variability will be calculated by performing the Fast Fourier transform, and respiratory sinus arrhythmia will also be calculated as previously described using the VU DAMS software. Additionally, plasma catecholamine measurements will include dopamine, norepinephrine, and epinephrine measurements. Plasma catecholamines will be assayed prior to and post stress. The 3-CAT high sensitivity kit will be used according to the manufacturer's protocol (Rocky Mountain Diagnostics, Colorado Springs, CO). This method has high sensitivity (limit of detection 25 pg/ml for NE), analytical specificity, and reproducibility (CVs <10%).

## Participant selection

We will recruit up to 30 subjects in order for 24 subjects to complete the study from the pool of >600 CAD patients from MIPS, all from Emory University-affiliated hospitals or clinics who have undergone rest/stress SPECT with mental stress. The inclusion and exclusion criteria have been published elsewhere. These patient have previously consented for future studies. Patients with previously demonstrated mental stress ischemia will be preferentially recruited, as such patients will likely benefit the most from the biofeedback intervention.

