### *Secondary objectives*

1. Study effects of biofeedback therapy on myocardial perfusion. **We hypothesize that the number of ischemic regions will decrease.**
2. Study the effects of biofeedback on peripheral vascular changes and biomarkers of sympathetic nervous system activation during mental stress. **We hypothesize that compared to controls, patients who undergo biofeedback (vs. usual care) will have less vasoconstriction (higher PAT ratio), lower resting catecholamine levels (norepinephrine, epinephrine and dopamine), and a reduced catecholamine stress response post-intervention vs. pre-intervention.**
3. Assess the relationship between stress-induced digital blood flow changes (PAT ratio), catecholamine increases, and changes in MBF before and after biofeedback intervention. **We hypothesize that compared to controls, patients with biofeedback therapy will have greater improvement in PAT ratio and lowest increases in catecholamines compared with baseline (pre-intervention).**
4. Assess the relationship between stress-induced endothelium dependent flow-mediated dilation (FMD) and arterial compliance (augmentation index and pulse wave velocity) and changes in MBF before and after biofeedback intervention. **We hypothesize that compared to controls, patients with biofeedback therapy will have greater improvement in FMD and arterial compliance.**

[figure not shown]

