## Study Design and Methods

### Overall Study Design

This pilot-study (Figure 1) will recruit 24 patients from the Mental Stress Ischemia Mechanisms and Prognosis Study (MIPS), a longitudinal cohort study which enrolled 695 patients between July 2009 and July 2014 with a diagnosis of stable CAD from Emory University-affiliated hospitals or clinics. Each patient completed baseline myocardial SPECT imaging, as well as psychosocial, hemodynamic and microvascular assessments, and blood was obtained for inflammatory, neurohormonal, and immunological biomarkers prior, during and after mental stress and conventional (exercise or pharmacological) stress. These patients have been followed on regular intervals with in-person clinic visits every year and by telephone every 6 months.

The patients will be randomized 1:1 to HRV biofeedback intervention for 6 weeks or wait-list control. Each group will undergo a rest/stress Rb PET imaging protocol (detailed below) similar to regular clinical imaging except that stress will be performed with a standardized

arithmetic mental stress test rather than pharmacological stress. We will hold beta-blockers for 48 hours and calcium channel blockers and nitrates on the day of the testing. It is standard protocol to hold anti-ischemic medications, including beta-blockers, ace-inhibitors, calcium channel blockers and nitrates, before exercise stress imaging studies, and this is the protocol followed by other nuclear cardiology studies.

Figure 2: Protocol

[figure not shown]

The full protocol is detailed in Figure 2.

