## Statistical analysis

In both intervention and control groups, we will calculate changes in MBF and myocardial flow reserve (MFR) with mental stress between baseline and the end of the protocol, and test whether the differences are different from zero. We will then compare the changes in MBF and MFR between the two randomization groups using mixed model regression analysis. If values are not normally distributed, appropriate transformations will be employed. If the two groups are not balanced for major characteristics despite randomization (demographic factors, comorbidities, lifestyle factors, etc.), these factors will be adjusted for in the analysis.

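### Prior mental stress ischemia is expected to shape benefit and is known before randomisation, but neither allocation nor a prespecified covariate uses it, and the ischemic-region hypothesis names no control comparison

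*Protocol*

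**What the plan says.** On enrichment, Participant selection states: "Patients with previously demonstrated mental stress ischemia will be preferentially recruited, as such patients will likely benefit the most from the biofeedback intervention". No minimum share is set. Status comes from the parent cohort (MIPS). The recruitment pool consists of patients "who have undergone rest/stress SPECT with mental stress", and Overall Study Design adds that "Each patient completed baseline myocardial SPECT imaging", in a cohort that "enrolled 695 patients between July 2009 and July 2014".

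On allocation, Overall Study Design says: "The patients will be randomized 1:1 to HRV biofeedback intervention for 6 weeks or wait-list control". The Abstract also gives 1:1, and neither place names a stratification factor. Power Calculations instead ends with 16 biofeedback and 8 control patients.

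On analysis, the Statistical analysis section computes changes in MBF and MFR in each arm and will "test whether the differences are different from zero". It then compares those changes between arms with a mixed model. Major characteristics are adjusted for only if they turn out unbalanced. The examples given are demographics, comorbidities and lifestyle, in an open-ended list that does not mention MSI.

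On ischemic regions, the hypothesis of secondary objective 1 reads in full: "We hypothesize that the number of ischemic regions will decrease".

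**The concern.** The sponsor expects one baseline feature to go with greater benefit, admits patients with and without it, and holds the result for each candidate before allocation. In a trial of 24, leaving that feature to chance and then choosing covariates after looking at the balance is weaker than using it in the allocation and the model from the start. A sizeable chance gap would make the MBF and MFR contrast hard to interpret, and an adjustment chosen after seeing the data would be open to challenge.

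The second problem is one of wording. Both arms repeat the subtraction task and the scan at week 6. A hypothesis that region counts fall, with no comparator, can be met by familiarity with the task or by measurement variation, with no contribution from biofeedback.

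**Working it through.** **Which allocation to use.** The plan gives no figure for MSI share or imbalance, so there is none to reproduce on the point itself. Its sample size does show which allocation the power table assumed. The inputs are MFR 1.38 vs 1.1 (25% of 1.1 is 0.275), SD 0.2 and power 0.8, with two-sided alpha 0.05 assumed because none is stated. A two-sample t-test then needs 20 in total at 1:1, as the table says, and 21 at 2:1. The other three rows (8, 26, 10) also match at 1:1. I therefore take 24 patients as 12 per arm and show 16 vs 8 afterwards.

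**Chance imbalance.** Let K of the 24 be MSI-positive and x of them fall in one arm of 12. Without stratification, P(x) = C(12, x) × C(12, K − x) / C(24, K), and the gap between arms is |2x − K|. A gap of 4 patients is 4/12 = 33 percentage points. K is not in the documents, so a range is shown.

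| K positive of 24 | P(gap of 4 or more) |
|---|---|
| 6 or 18 | 2 × 10,428 / 134,596 = 15.5% |
| 8 or 16 | 2 × 70,983 / 735,471 = 19.3% |
| 12 | 2 × 297,926 / 2,704,156 = 22.0% |
| 20 | 2 × 495 / 10,626 = 9.3% |
| 21 or more | 0 (at most 3 negatives, so the gap is at most 3) |

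The even mix gives the highest figure shown. At 16 vs 8, the chance of a gap of at least 33 points is 12.9% (K = 6 or 18), 6.5% (8 or 16) and 19.3% (12). At that allocation, a gap of at least 25 points has a 36.3% chance with K = 8 or 16.

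**After stratification.** At 1:1, permuted blocks of 2 or 4 within each stratum limit the gap to 1 or 2 MSI patients. That is 1/12 = 8 or 2/12 = 17 points, so a 33-point gap cannot occur.

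**Comparator wording.** The hypotheses of secondary objectives 2, 3 and 4 each set biofeedback against controls, while that of objective 1 does not. The Statistical analysis section does not fill the gap, because its between-arm comparison covers MBF and MFR only. If regions fell equally in both arms, the between-arm difference would be zero, yet the hypothesis as worded would be met.

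**The case against.** Much can be said for the plan.

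- **Silence on stratification.** A 1:1 ratio does not exclude stratified allocation, and a randomisation plan not shown may provide it. Stratifying a 24-patient pilot is also optional. This stands as a limit. If strata already exist, only the covariate rule needs changing. That rule is in the Protocol, and it makes adjustment depend on observed imbalance.
- **Existing safeguards.** A reader might infer that no between-arm test or imbalance provision exists. The Statistical analysis section has both, and its open list could include MSI. The weakness is that MSI is not named and the choice follows the data.
- **Likely mix.** Filling 30 places needs 30/600 = 5% of the pool, so the positive share may be high and the risk small or nil. That is fair, and it is why the range runs down to zero.
- **Comparator evident elsewhere.** The Abstract sets the study aims against usual care, and the primary hypothesis names wait-listed controls. The defect is therefore confined to the wording of one secondary objective. The stress task also varies its starting numbers and difficulty, which may limit familiarity but does not exclude it.
- **Patients with no region at baseline.** A reader might infer that they can only dilute the result and should be excluded. They can gain regions, so they still inform the contrast. Selecting on a noisy baseline PET also invites regression to the mean. If half had none, the analysis would drop from 24 to 12.
- **Age of the SPECT result.** It is tempting to call the label invalid. The documents show that it is older and from another modality, not that it is wrong, and every patient has a baseline mental-stress PET.

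**Conclusion.** The point holds in a limited form. The Protocol leaves a feature that it expects to matter, and already holds, to chance allocation and after-the-fact adjustment. The chance of a 4-patient gap at 12 per arm runs from 22% to nil, depending on an MSI share that the documents do not give. The calculation assumes unstratified allocation of exactly 24 patients.

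Stronger readings are not supported. The sponsor says only that MSI patients are likely to benefit most, not that MSI determines benefit. Imbalance under randomisation is chance, not bias. Nor do the documents say that patients without MSI gain nothing, so a loss of power on the primary outcome cannot be put forward as a finding.

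The missing comparator in secondary objective 1 is a plain textual defect, small in scope. Both matters should be corrected because the remedy is cheap, but neither undermines the trial.

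**What to change.** 1. Stratify the randomisation by MIPS MSI status (yes/no) with small permuted blocks, and include that status as a prespecified covariate whatever the observed balance. Fit the blocks to whichever allocation stands once 1:1 (Abstract, Overall Study Design) and 16 vs 8 (Power Calculations) are reconciled. The strata must be set before the first patient is randomised. If that has passed, the prespecified covariate remains possible.
2. Restate secondary objective 1 as a between-arm comparison of the baseline-to-week-6 change in number of ischemic regions, in all randomised patients, adjusted for the baseline count. Keep patients with at least one region at baseline as a supportive analysis only.
3. State that within-arm tests against zero are descriptive and support no efficacy claim.

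The cost is a two-stratum allocation list from data already held, one extra model term, and a few sentences of wording.

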## Statistical analysis

In both intervention and control groups, we will calculate changes in MBF and myocardial flow reserve (MFR) with mental stress between baseline and the end of the protocol, and test whether the differences are different from zero. We will then compare the changes in MBF and MFR between the two randomization groups using mixed model regression analysis. If values are not normally distributed, appropriate transformations will be employed. If the two groups are not balanced for major characteristics despite randomization (demographic factors, comorbidities, lifestyle factors, etc.), these factors will be adjusted for in the analysis.

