## Power Calculations

The table shows a range of sample sizes needed to achieve a power of 0.8-0.9 with an effect size of 25% to 50% improvement in MS-MFR (an improvement of 25% would be deemed clinically significant). A sample size of 20 would achieve at least 80% power with an effect size of 25%. Because some patients may drop out, we plan to increase the sample size by 20%, bringing the final sample size to 24, with 16 in the Biofeedback group and 8 in the Control group.

Table. Sample size determination and power.  
(BF=Biofeedback, C=Control)

| BF Group
MFR | Control
Group MFR | SD  | Power | Improvement in MS-
MFR | Total n |
|-----------------|----------------------|-----|-------|---------------------------|---------|
| 1.38            | 1.1                  | 0.2 | 0.8   | 25%                       | 20      |
| 1.65            | 1.1                  | 0.2 | 0.8   | 50%                       | 8       |
| 1.38            | 1.1                  | 0.2 | 0.9   | 25%                       | 26      |
| 1.65            | 1.1                  | 0.2 | 0.9   | 50%                       | 10      |

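### The primary comparison uses changes without a fixed baseline MS-MFR covariate, while the power table is built on MFR levels; fixing baseline adjustment and closing the covariate list is a nearly free gain in efficiency

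*Protocol*

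**What the plan says.** Protocol, Statistical analysis: changes in MBF and MFR are first tested against zero within each arm. Then comes the randomised comparison: "We will then compare the changes in MBF and MFR between the two randomization groups using mixed model regression analysis". The structure of the mixed model is not described and baseline MS-MFR is not listed as a covariate. On other covariates the section begins "If the two groups are not balanced for major characteristics despite randomization", gives examples from three broad classes closed by an etc., and says these will be adjusted for. It gives no criterion for imbalance.

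Protocol, Power Calculations: "A sample size of 20 would achieve at least 80% power with an effect size of 25" (per cent). The table's columns are the MFR of each group, an SD, the power, the improvement and the total n. The row behind the chosen size reads "1.38 | 1.1 | 0.2 | 0.8 | 25% | 20". The section gives no SD of change, no correlation between visits, no alpha and no sidedness.

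**The concern.** The analysis is described in terms of changes and the sample size in terms of levels. The two have the same SD only at one particular correlation between visits, and the protocol does not give that correlation. If it is low, subtracting the baseline adds noise, and the trial has less power than the table says. Using the same baseline value as a regression covariate avoids this, and every patient already has a baseline PET study.

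The covariate rule is a separate matter. With about 20 to 24 patients some imbalance is almost certain to be visible. With no threshold and no closed list, the primary model would be chosen after the data are seen.

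**Working it through.** **Inputs.** From the power table: means 1.38 and 1.1, SD 0.2, total n 20. The difference is 0.28 as printed, or 0.275 if it is exactly 25% of 1.1; I use 0.275 below. From the design text: "The patients will be randomized 1:1 to HRV biofeedback intervention for 6 weeks or wait-list control". The Power Calculations section instead gives 16 and 8, so both splits are shown. Completers: 20 (power section) or 24 (Participant selection, which recruits up to 30 so that 24 complete). Assumptions: two-sided alpha 0.05; 0.2 is the SD of MFR at one visit, equal at both visits; correlation ρ between baseline and week 6, not given, so shown over a range.

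**Reproducing the table.** A two-sample t-test on levels (noncentral t, equal arms, SD 0.2) with differences of 0.275 and 0.55 gives total n of 20, 8, 26 and 10, which matches all four rows. At 10/10 the power is 83% (84% with 0.28). So the table is a comparison of single-visit levels with no use of baseline.

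**SD under each analysis.**
- Change score: 0.2 × √(2(1 − ρ)). At ρ = 0.3 this is 0.2 × √1.4 = 0.237; at ρ = 0.5 it is 0.2 × √1 = 0.200.
- Baseline-adjusted residual: 0.2 × √(1 − ρ²). At ρ = 0.3 this is 0.2 × √0.91 = 0.191; at ρ = 0.5 it is 0.2 × √0.75 = 0.173.

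**Power, difference 0.275.** The adjusted column gives the noncentral-t value with one degree of freedom charged for baseline, then the simulated value. Simulation is a little lower because it also carries the cost of chance baseline imbalance.

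| Split | ρ | Change score | Baseline-adjusted (formula / simulated) |
|---|---|---|---|
| 10/10 | 0 | 54% | 83% / 80% |
| 10/10 | 0.3 | 69% | 86% / 84% |
| 10/10 | 0.5 | 83% | 92% / 90% |
| 10/10 | 0.7 | 96% | 98% / 97% |
| 13/7 | 0 | 50% | 79% / 76% |
| 13/7 | 0.3 | 65% | 83% / 80% |
| 12/12 | 0.3 | 78% | 92% / 91% |
| 16/8 | 0.3 | 73% | 89% / 87% |
| 16/8 | 0.5 | 86% | 94% / 93% |

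**Smallest ρ at which the change score reaches 80%** (difference 0.275; value for 0.28 in brackets): 10/10, 0.46 (0.44); 13/7, 0.51 (0.49); 12/12, 0.34 (0.32); 16/8, 0.41 (0.39).

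**The case against.** **The model may already do this.** With two imaging visits, an unconstrained mixed model gives the same comparison as the change score, but one that constrains the arms to a common baseline behaves like baseline adjustment. The protocol does not say which is meant, and model form is often left to a statistical analysis plan. This stands as a limit on the point: the text describes a comparison of changes, and an unadjusted change score is a reading of it.

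**The shortfall rests on unstated inputs.** If 0.2 were the SD of change, the change-score plan would have the tabulated power at any correlation. The column headings ("BF Group MFR | Control Group MFR | SD | Power | Improvement in MS- MFR | Total n") favour a single-visit SD, but nothing says so. This stands too, and is why the SD needs a label.

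**Stronger readings that do not hold.**
- A reader might infer that a change-score comparison is biased or invalid. Under randomisation it is neither.
- A reader might take ρ = 0.5 as the point below which the stated power is lost. That is where the SD of change equals 0.2; the 80% thresholds are those listed above, and only 13/7 is close to 0.5.
- A reader might infer that baseline adjustment always secures 80%. At 13/7 with ρ = 0 it gives about 76 to 79%.
- A reader might say that imbalance-triggered adjustment costs power. That depends on the factors. With six independent candidates, a 0.5 SD trigger and ρ = 0.5, non-prognostic factors take change-score power from about 90% to 83% (12/12) and 86% to 78% (16/8). If each factor correlates 0.3 with the outcome there is no loss (90% to 91%; 86% to 87%), and type I error stayed between 2.7% and 5.0% in these runs. The objection to the rule is the discretion it leaves.
- A reader might see the within-arm tests as a substitute for the comparison between arms. The protocol goes straight on to that comparison and does not propose contrasting one significant arm with one non-significant arm.

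**Conclusion.** The point holds as a worthwhile improvement to a valid analysis. At every correlation examined from 0 to 0.7 and at every split, adjusting for baseline MS-MFR has more power than the unadjusted change score. The gap is about 15 percentage points at 10/10 with ρ = 0.3 and about 7 at ρ = 0.5, using the simulated adjusted values, and it narrows as ρ rises. Whether the planned comparison misses 80% depends on the correlation, on 0.2 being a single-visit SD, on how many patients complete and on which allocation is used; the protocol leaves the first two open and contradicts itself on the last two. The open covariate rule stands on its own: it has neither a criterion nor an end to its list, so the primary model is not fixed before the data are seen.

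**What to change.** In Statistical analysis, define the primary comparison as week-6 global MS-MFR on arm with baseline MS-MFR as a fixed covariate (ANCOVA, or the equivalent mixed model with a common baseline), and treat MBF in the same way. Replace the imbalance-triggered rule in the primary model with a covariate list fixed before any outcome is examined by arm. The list may be baseline alone, since the documents do not show that any other factor predicts MS-MFR. Keep imbalance-driven adjustment, if wanted, as a sensitivity analysis.

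In Power Calculations, say whether 0.2 is the SD of a level or of a change, state alpha and sidedness, and give the correlation assumed if changes are kept. Reconcile 1:1 with 16/8, and 20 with 24 completers, because both move the thresholds.

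The cost is wording and one degree of freedom for baseline. No new data are needed.
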